### 1.2. Objectives

The use of equations to estimate body composition is a frequent strategy since it represents a doubly indirect method with a good correlation to the methods mentioned above. However, this leads to the question of whether current WG-based equations are valid for estimating fat mass and fat-free mass in the Colombian population with different levels of physical activity? On the other hand, would it be advantageous to develop new models to obtain a specific equation for the Colombian population? Thus, the aim of this study will be twofold: (i) externally validate the current WG-based equations to estimate fat mass and fat-free mass as compared with DXA, and (ii) develop new models to estimate fat mass and fat-free mass using the WG as a predictive variable, and subsequently validate the new equations in the Colombian population with different levels of physical activity.

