## 2. Methods

### 2.1. Study Design

This will be a cross-sectional study based on the Strengthening the Reporting of Observational Studies in Epidemiology–Nutritional Epidemiology (STROBE–nut) guidelines, an Extension of the STROBE Statement [41]. This study (the F20 Project) will test the validity of current WG-based equations and will develop new models to estimate fat mass and fat-free mass as compared with DXA as a reference criterion.

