#### 2.5.2. Anthropometry

All anthropometric measurements will be carried out in accordance with the International Standards for Anthropometric Assessment published by the ISAK [12]. Body mass will be measured with a digital scale to the nearest 100 g (Seca 874, Hamburg, Germany). A portable stadiometer with a 1 mm graduation will be used to measure stature and wingspan (Seca 213, Hamburg, Germany). A 50 cm high wooden anthropometric box will be used to measure the sitting height. The skinfold thicknesses will be measured with a calibrated skinfold caliper (Harpenden, UK). Girths will be measured with a non-extensible metal tape with a thickness of 0.7 cm (Lufkin w606PM, Apex Tool Group, Sparks, MD, USA). The measurement of breadths will be performed with a Realmet Petit (16 cm) small sliding caliper (Realmet, Barcelona, Spain). Averages based on two measurements of anthropometric data will be calculated and analyzed.

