### 2.6. Bias

The different types of intentional or unintentional bias and error that may occur in this study will be controlled according to their nature: (i) Gross errors—daily calibrated, certified, and recognized by international entities or Colombian technical regulations and legal metrology (Superintendence of Industry and Commerce) equipment and instruments will be used; (ii) Pre-analytical errors (blunders)—the research assistance personnel will be previously trained in the annotation and accompaniment at the moment of recording the data using a specific typography and computer files for databases. The recorder assistant will always repeat the value dictated by the anthropometrist at the time of the assessment; (iii) Systematic errors—the relative technical error of measurement of the technicians will be reported. We will ensure that the intra-observer technical error of measurement of the certified anthropometrists (√[∑differences^2^/2n]) will be less than 7.5% for skinfolds and less than 1.5% for the other measurements, which is considered acceptable by the ISAK recommendations [10]. The coefficient of variation of the DXA equipment will be reported (CV% = Standard Deviation/Average × 100%). The test–retest reliability of the DXA unit that will be used in this study has shown a coefficient of variation ranging from 1.0 to 2.0%. In addition, similar to previous reports [46], we will adjust the DXA measurements based on the model proposed by Heymsfield et al. [51] to eliminate the influence of fat-free adipose tissue (FFAT) on DXA-derived fat-free mass. This has been shown to provide more accurate values to detect changes in body composition [52]. Therefore, we will estimate the adipose tissue as DXA-fat mass ÷ 0.85; FFAT will be then calculated as adipose tissue × 0.15; and, finally, DXA-derived fat-free mass will be adjusted with the subtraction of FFAT.

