### 2.7. Study Size

According to Knofczynski and Mundfrom [53], to obtain (at least) a coefficient of determination (R^2^) of 0.5 with an excellent level of prediction using 3 independent variables, a total of 130 participants will be needed. Stratified probability sampling techniques will be used. Thus, the total number of participants will be divided into three strata following optimal allocation methods. A fixed cost has been assigned for each stratum (sedentary persons, C1; physically active subjects, C2; and athletes, C3, given that C3 > C2 > C1) to calculate the sample size of each population using Lagrange multipliers, given by the expression:(1)$$nh=n\;\frac{NhSh/\surd Ch}{\sum_{h=1}^{L}NhSh/\surd Ch},\;h=1,\;2,\;\ldots ,\;L$$
where, the values of *n_h_* correspond to the sample units for each stratum, *N_h_* is the maximum number of participants allowed, *C_h_* is the constant cost in all strata, *L* is the number of strata, and *S_h_* is the population quasi-variance of stratum *h*. The values obtained for the sedentary group are *n* = 54; for the physically active population group, *n* = 43; and for the athlete group, *n* = 33. To validate the new equation, the development/validation ratio will be 70/30 over the number of subjects participating in the study.

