### 2.8. Statistical Methods

The descriptive analysis of the anthropometric characteristics of the study population will be reported as means, standard deviations, and 95% confidence intervals. First, the total sample of participants will be used for the external validation of the RFM (to estimate whole-body-fat percentage) [26] and the Takai et al., equation (to estimate fat-free mass) [35]. A correlation analysis will be performed by calculating Pearson’s r, intraclass correlation coefficient (ICC), concordance correlation coefficient (ρ_c_), adjusted coefficient of determination (aR^2^), and root mean squared error (RMSE) as compared to DXA measurements. Smaller values of standard error of the estimate (SEE) and RMSE will indicate that the estimated values are closer to the DXA measurements. Bland–Altman diagrams will be used for the concordance analysis. This is a procedure to determine whether two measurement methods, X and Y, agree sufficiently to be declared interchangeable (D = X − Y). The mean of these differences represents the systematic error (bias), while the variance of these differences (1.96 SD) measures the dispersion of the random error.

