The development of the new equations to estimate fat mass (dependent variable) from different combinations of WG with sex, physical activity level, body mass, and stature (as predictor variables) will be carried out with multiple regression models under traditional (Ordinary Least Squares method) and Bayesian approaches (limited to three independent variables). For the latter, the ‘bayesbr’ and ‘bayes.lm’ R packages will be used. Variance inflation factors will be used to detect multicollinearity among predictors in the multiple linear regression models, and autocorrelation in the residuals will be assessed through the Durbin–Watson test. The variation explained by the model will be determined by the aR^2^. Finally, the SEE will be calculated for all generated models to measure the regression’s precision, while the RMSE will be used to evaluate how close the estimated values from each equation are to the actual measured values as reported elsewhere [42]. All possible regression models will be ranked using the akaike information criterion (AIC), the Bayesian information criterion (BIC), the Mallows’ C_p_, and the Hocking’s Sp. After compliance with all of the assumptions of the multiple regression analysis (normality of residual errors will be confirmed with the Omnibus k-squared and Jarque-Bera tests), the model with the better performance that includes WG will be selected for further analysis. The predictability of the equation in the selected model will be tested in the validation sample by calculating the aR^2^, RMSE, CCC, and ICC with its respective 95% CI. The concordance analysis will be performed by means of Bland–Altman diagrams, reporting the concordance intervals at 95%. Statistical tests will be carried out using the SPSS v26 statistical package (IBM Corp., Armonk, NY, USA) and the latest version of the environment for statistical computing R [54].

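### Objective (ii) promises new equations for fat mass and fat-free mass, but section 2.8 develops, selects and validates one for fat mass only

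*Protocol article*

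**What the plan says.** All references are to the protocol article.

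- Section 1.2 (Objectives), aim (ii): "develop new models to estimate fat mass and fat-free mass using the WG as a predictive variable", followed by validation of the new equations.
- Section 2.1 (Study Design) repeats both outcomes: the study "will develop new models to estimate fat mass and fat-free mass as compared with DXA as a reference criterion". Section 4 (Conclusions) also expects a tool that serves both compartments.
- Section 2.8 (Statistical Methods), on model development: "The development of the new equations to estimate fat mass (dependent variable) from different combinations of WG" and further predictors. After ranking, one model is chosen, and "The predictability of the equation in the selected model will be tested in the validation sample".
- Section 2.7 (Study Size) also speaks of one equation: "To validate the new equation, the development/validation ratio will be 70/30 over the number of subjects participating in the study".
- Section 2.8 mentions FFM only for the external validation of the existing athlete equation, in the words "equation (to estimate fat-free mass". That belongs to aim (i).
- Section 2.6 (Bias) defines the FFM reference: adipose tissue is DXA fat mass divided by 0.85, FFAT is 0.15 of that, and "DXA-derived fat-free mass will be adjusted with the subtraction of FFAT".

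**The concern.** Which outcome is modelled is a core element of a prediction study. The article does not leave it open for a later document. It fixes the dependent variable, and that choice conflicts with its own objective.

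The stake is the second product of the study. Section 1.1 presents the existing FFM equation as one developed for male athletes. A new FFM equation is what the study offers women and non-athletes if the existing one does not carry over to them. Under section 2.8 as written, no such equation is fitted, chosen or tested. If the route to FFM is picked only after the data are seen, a stated objective will rest on an unplanned analysis.

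**Working it through.** The point is mainly a comparison of texts. The plan gives no figure of its own to reproduce here; its sample size of 130 is not in question.

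**Step 1. Promise against analysis.**

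| | FM | FFM |
|---|---|---|
| New model promised (1.2, 2.1) | yes | yes |
| Dependent variable in model development (2.8) | yes | no |
| Model selected and tested in the validation sample (2.8) | yes, one | no |
| Derivation from the other outcome stated | not needed | no |

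The plural (equations) in section 2.8 does not supply the second outcome. It is tied to fat mass and to the different predictor combinations.

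**Step 2. Can FFM be obtained from an FM equation?** Inputs are the section 2.6 formulas and measured body mass (section 2.5.2: "Body mass will be measured with a digital scale to the nearest 100 g"). Assumptions: FM is in kg, which section 2.8 does not say, and DXA FFM = body mass − FM, that is, two compartments with bone counted in FFM and DXA total mass equal to scale mass.

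- FFAT = 0.15 × (FM/0.85) = 0.1765 × FM
- Adjusted FFM = body mass − FM − 0.1765 × FM = body mass − FM/0.85

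For an illustrative FM of 20 kg, FFAT = 0.15 × 23.53 = 3.53 kg, and adjusted FFM = body mass − 23.53 kg. So FFM on the plan's own scale follows from an FM equation.

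**Step 3. Does FM accuracy carry over?** The derived FFM error is the FM error multiplied by −1/0.85. Its standard error of estimate (SEE) in kg is therefore 1/0.85 = 1.176 times that of FM.

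**Step 4. Does the derived equation match a directly fitted one?** It does if body mass is a linear predictor: least squares then reproduces body mass exactly, so the direct fit is body mass − (predicted FM)/0.85. Without body mass as a linear term, the two can differ. That case is realistic, because section 3 expects the ratios of body mass to waist girth (WG) and of WG to stature in the best model.

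**Step 5. Illustration on simulated data.** The population values are assumed and do not come from the article; n = 91, the development share (0.7 × 130).

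| Predictors | FM SEE (kg) | Derived FFM SEE (kg) | Direct FFM SEE (kg) |
|---|---|---|---|
| WG, sex, body mass | 2.59 | 3.05 | 3.05 |
| WG, sex, stature | 2.91 | 3.43 | 4.02 |

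In 500 such samples, the best three-predictor subset (lowest SEE; candidates WG, sex, body mass, stature and the two ratios) differed between FM and FFM in about 19%. These figures show only that model choice and accuracy for FM do not settle those for FFM. They do not forecast this study's results.

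**The case against.** The strongest reply is that this is abbreviated wording in a condensed article, not a decision to drop FFM. Section 4 expects a tool for both compartments. The two ratios that section 3 expects in the best model are those used in the existing FFM equation described in section 1.1. A fuller document may name the second outcome. In addition, all the data are collected, the methods in section 2.8 transfer unchanged to FFM, FFM can be derived from FM, and aim (i) for FFM is untouched.

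Most of this stands as a limit on the consequence. It does not remove the contradiction, because the published text names its dependent variable and that name leaves out half of aim (ii). Signs that an FFM model was intended make the correction more necessary.

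Three stronger readings are tempting, and the article does not support them:

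- A reader might infer that the FFM part of the objective cannot be answered. It can, with one more model or a stated derivation.
- A reader might infer that subtracting FFAT makes FFM unrecoverable from FM. Section 2.6 makes FFAT a fixed multiple of FM, so step 2 recovers it.
- A reader might infer a mismatch of 0.176 × FM (3.5 kg at 20 kg of fat) between predicted and reference FFM. It would arise only if unadjusted FFM were compared with the adjusted reference, and the article proposes no such comparison.

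**Conclusion.** The point holds as an internal contradiction. Sections 1.2 and 2.1 promise new equations for two outcomes, and section 2.8 specifies one. Development, selection and validation of a new FFM equation are absent from the analysis as written. Sampling, measurement and the external validation of existing equations are not affected.

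The derivation softens the consequence but does not close the gap, since the article neither states nor tests it. The factor of 1.18 on the error rests on FM in kg and on DXA FFM being equal to body mass minus FM; any difference between scale mass and DXA mass would add to it. The text should be corrected before analysis.

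**What to change.** Choose one of three changes:

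1. In section 2.8 name two dependent variables, DXA fat mass (kg) and DXA fat-free mass (kg), with the same candidate predictors, selection rule and validation statistics for each. Put FFM on the FFAT-adjusted scale of section 2.6, or state and justify another scale and use it throughout. Switching to unadjusted FFM in this section alone would create a new conflict with section 2.6.
2. State that FFM is derived as body mass − (predicted FM)/0.85, and validate that derived value against the section 2.6 reference in the validation sample.
3. Restrict objective (ii) to fat mass, and align sections 2.1 and 4 with it.

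Option 1 costs wording and one more model run on data already planned. Option 2 costs wording and one more validation table. Option 3 costs wording only, but gives up the new FFM equation.

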Several authors have concluded that regression equations that use WG as a predictive variable appear to estimate body fat percentage more accurately [23,24,25]. In this sense, the relatively recent efforts of some research groups have developed equations that include WG as an independent variable to estimate fat mass and fat-free mass. On the one hand, Woolcott and Bergman [26] developed and validated a simple equation, named relative fat mass (RFM), to estimate the percentage of total body fat using the WG, stature, and sex of the American adult population (64 − (20 × (stature [m]/WG [m])) +  (12 × sex [0 for male and 1 for female])). The population data were extracted from the National Health and Nutrition Examination Survey (NHANES) between 1999 and 2006. The performance of RFM as an easy and useful tool in clinical practice, with a better correlation to DXA than BMI (RFM: R^2^ = 0.84; RMSE = 3.51% vs. BMI: R^2^ = 0.36; RMSE = 7.04%) has been validated in adults [27], children between 8 and 14 years old, and adolescents between 15 and 19 years old [28], obese subjects [29,30], and individuals with Down syndrome [31], among other populations at cardiovascular risk [32,33]. It is worth noting that the RFM defines obesity according to the cutoff points of the DXA measurements, to the point that following the rounded thresholds of the RFM baseline, the current recommendation for diagnosing obesity and predicting the risk of death with this parameter is 40% for women and 30% for men [34]. On the other hand, Takai et al. [35] developed an equation to estimate fat-free mass in male athletes using some indices as independent variables, including WG/body mass and stature/WG. The equation developed by these authors was validated with a sample of 48 athletes from different disciplines and showed a high correlation (R^2^ = 0.900, SEE = 2.3 kg [3.8%]) with the fat-free-mass data obtained by DXA (FFM (kg) = 0.883 × Body mass/WG [kg/m] + 43.674 × WG/Stature [cm/cm] − 41.480). The results of this study demonstrated that an equation using body mass and stature ratios with WG as independent variables is applicable and useful for predicting fat-free mass in male athletes.

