## 3. Expected Results

Diagnosing nutritional status generally involves the use of two indicators—body mass and stature—which, although necessary, cannot define body composition accurately. Currently, WG is used as a better predictor of cardiovascular risk and central obesity. Interestingly, scientific evidence supports the predictive potential of WG given the high correlation of WG-based equations with more reference methods (e.g., DXA and CT) for the assessment of body composition. However, these also have limitations that are mainly due to differences with respect to the population on which they have been developed since they are specific and, given the fluctuations that occur in age and sex, further external validation is warranted [40,55]. Development and validation of new models will increase generalizability and scientific soundness at the time of evaluating body composition in the Colombian population with different levels of physical activity. Thus, future research like this should take advantage of the predictive potential of WG together with other basic measurements (body mass and stature) to estimate with a low rate of error the fat mass and fat-free mass in different populations. Importantly, evaluating the performance of new models with different combinations of several variables (e.g., age, sex, body mass, stature, and WG) raises its relevance. Based on the available literature, we expect to find, after model specification, the body-mass-to-WG and WG-to-stature ratios as part of the best regression model. The body-mass-to-WG ratio has been previously found to have a strong correlation with body composition across the lifespan [56,57]. On the other hand, the WG-to-stature ratio has been reported as a better predictor of abdominal-fat distribution in men compared to BMI or the WG-to-hip ratio using computed tomography as a standard method [58]. In fact, some recent research suggests the WG-to-stature ratio is a strong predictor of abdominal obesity with no relevant age- or sex-dependent effects [59,60,61,62].

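### No recalibrated RFM is planned beside the locally fitted fat-mass equation, so a local offset in RFM could be mistaken for the benefit of a new model

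*Protocol article*

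**What the plan says.** All references are to the protocol article.

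- **The existing equation.** Section 1.1 gives RFM with fixed constants, beginning "64 − (20 × (stature [m]/WG [m", and says it was developed "using the WG, stature, and sex of the American adult population". It quotes the performance as "RFM: R^2^ = 0.84; RMSE = 3.51" (per cent).
- **Step one of section 2.8.** The existing equation is tested as published: "the total sample of participants will be used for the external validation of the RFM". Pearson's r, ICC, concordance correlation, adjusted R² and RMSE are listed, followed by Bland–Altman plots, for which "The mean of these differences represents the systematic error (bias").
- **Step two of section 2.8.** A new equation for fat mass is developed "from different combinations of WG with sex, physical activity level, body mass, and stature (as predictor variables"), with all its coefficients estimated from the study data. The selected model is tested in the validation sample.
- **The question behind both steps.** Section 1.2 asks: "would it be advantageous to develop new models to obtain a specific equation for the Colombian population"?
- **The expected weakness of existing equations.** Section 3 says "these also have limitations that are mainly due to differences with respect to the population on which they have been developed".

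No section recalibrates RFM by intercept, by slope or by refitting its form.

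**The concern.** The two equations do not get equal treatment. The new one takes its constant and slopes from these participants, this DXA unit and these waist measurements. RFM takes nothing from them. The article expects population-specific error in existing equations, and its Bland–Altman step will estimate the average size of that error, but the estimate is not used to update RFM.

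RMSE combines offset and scatter. Suppose the new equation shows a lower RMSE than published RFM. Part of the difference may be local calibration, which needs one or two constants. The rest may be a real gain from a different model. Without an updated RFM the two parts cannot be told apart in the validation sample, although the question in section 1.2 turns on the second. Section 4 hopes the resulting equations will be adopted by the Colombian health system, so it matters whether a new equation was needed or a corrected existing one would have served.

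**Working it through.** **Sample figures (section 2.7).** 54 + 43 + 33 = 130, and a 70/30 split gives 91 and 39. Both agree with the article. The 130 comes from a cited source that is not in the documents and cannot be re-derived here. This point does not depend on it.

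**Can the stated candidates return a recalibrated RFM?** In kilograms, RFM is body mass × (64 − 20 × stature/WG + 12 × sex)/100. That needs the products mass × stature/WG and mass × sex. WG, sex, activity, mass and stature entered as separate terms do not reproduce it. Nor do the two ratios expected in section 3 (body mass/WG and WG/stature), though WG/stature with sex comes near the RFM form.

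**Effect of an offset, fat-% scale.** Inputs: scatter SD = 3.51 (the RMSE in section 1.1, taken as pure scatter, which is an assumption) and offset b, which is not in the documents and is assumed to be 0 to 4 points. For published RFM, RMSE = √(3.51² + b²). After estimating p constants in 91 people, RMSE ≈ 3.51 × √(1 + p/91).

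| b | Published RFM | RFM + constant (p = 1) | Reduction |
|---|---|---|---|
| 0 | 3.51 | 3.53 | none |
| 1 | 3.65 | 3.53 | 3% |
| 2 | 4.04 | 3.53 | 13% |
| 3 | 4.62 | 3.53 | 24% |
| 4 | 5.32 | 3.53 | 34% |

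Intercept plus slope (p = 2) gives about 3.55. The standard error of the constant is 3.51/√91 = 0.37 points.

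**Which equation then does better?** This was checked by simulation, 4,000 runs per setting, split 91/39, with every equation scored in kg on the same 39. Assumed anthropometry:
- equal sexes; stature 1.60 m (women) and 1.73 m (men), SD 0.065;
- BMI 24.5, SD 3.5;
- WG 0.74 m (women) and 0.83 m (men), plus 0.021 m per BMI unit, SD 0.035.

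Fat % = RFM + b + g × (BMI − 24.5) + noise with SD 3.51. The new equation is the best fit among WG, sex and mass; WG, sex and stature; and WG/stature, sex and mass. The refit re-estimates the constants on stature/WG and sex.

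| b, g | Published RFM (kg) | RFM + constant (kg) | Refit (kg) | New (kg) | New beats published | New beats RFM + constant | New beats refit |
|---|---|---|---|---|---|---|---|
| 0, 0 | 2.41 | 2.42 | 2.45 | 2.57 | 14% | 14% | 18% |
| 1, 0 | 2.51 | 2.43 | 2.46 | 2.58 | 36% | 14% | 18% |
| 2, 0 | 2.77 | 2.42 | 2.45 | 2.57 | 79% | 15% | 17% |
| 3, 0 | 3.18 | 2.42 | 2.45 | 2.57 | 97% | 15% | 18% |
| 4, 0 | 3.67 | 2.43 | 2.45 | 2.58 | 100% | 14% | 17% |
| 2, 0.3 | 2.96 | 2.53 | 2.48 | 2.58 | 89% | 38% | 25% |
| 2, 0.6 | 3.31 | 2.84 | 2.58 | 2.63 | 96% | 80% | 41% |

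Other assumed settings, from separate simulations:
- With both ratios from section 3 offered as candidates (600 runs, b = 3, RFM form true), the new equation averages 2.56 kg against 2.43 kg for RFM + constant and wins in 18% of runs. Without the ratios the figures are 2.68 kg, 2.44 kg and 9%.
- With an activity effect of +2/0/−4 points that RFM misses (sedentary, active, athlete), the new equation beats RFM + constant in about half of runs (51% in one simulation, 49–63% across offsets in another).
- With fat mass truly additive in kg, the new equation is better on average (2.67 against 3.03 kg).

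**Fat-free mass in athletes.** Section 2.6 subtracts fat-free adipose tissue, fat mass/0.85 × 0.15 = 0.176 × fat mass, from DXA fat-free mass. Section 1.1 mentions no such adjustment for the published fat-free-mass equation. If the adjusted value is the reference, an assumed athlete fat mass of 8 to 12 kg shifts it by 1.4 to 2.1 kg. Treated as a pure offset on that equation's SEE of 2.3 kg, this gives √(2.3² + 1.41²) = 2.7 to √(2.3² + 2.12²) = 3.1 kg.

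**The case against.** The strongest reply is that the plan contains no contest between the two equations. RFM is validated for fat percentage in the total sample. The new equation predicts fat mass and is tested in the validation sample. No section names RFM as comparator or sets a rule for calling the new equation better. The two aims in section 1.2 are to validate and to develop, not to show superiority. This stands. A reader might infer that the plan will report a calibration offset as an advantage, but the document does not commit to that reading. It only leaves it open.

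Second, the offset would not be hidden. The Bland–Altman mean difference shows it, and Pearson's r is unaffected by a constant shift. This also stands, but only in part: those figures show that RFM is biased, not whether a corrected RFM would match the new equation in the validation sample.

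Third, a reader might infer that recalibrated RFM would be the more accurate equation. The documents do not support that. The size of any offset and the truth of the RFM form are both assumed. With no offset, published RFM usually wins unless body mass or activity adds information. The expected ratio terms narrow the deficit. Where body mass or activity matters, the new equation can win, and 76 of the 130 participants (43 + 33) are active or athletes.

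Finally, developing a new equation is a legitimate stated aim and a condensed article may omit detail. That lowers the weight of the point. It does not remove it, because section 2.8 sets out the sequence, candidates and selection criteria, and the point concerns that stated sequence.

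**Conclusion.** The point holds as a conditional one. RFM keeps its US constants, the new equation is fitted locally, and no recalibrated RFM is planned. An assumed offset of 2 to 4 fat-% points raises published RFM's RMSE by 15% to 52% (3.51 to between 4.04 and 5.32). One constant removes nearly all of that. If the RFM form is true, such offsets let the new equation beat published RFM in 79–100% of simulated studies and recalibrated RFM in only about 15%. If BMI adds 0.6 points per unit, it beats RFM + constant in about 80% but the refitted RFM form in only about 40%. The comparison therefore does not prejudge the answer.

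These results rest on the assumed offset, the assumed anthropometry and the use of 3.51 as scatter. They show that the planned outputs cannot separate calibration from real model gain. They do not show that a new equation is unnecessary, and nothing planned becomes invalid.

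**What to change.** In section 2.8, after the external-validation step, add model updating in the development sample:

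1. RFM + constant.
2. a + b × RFM.
3. A refit with stature/WG and sex.
4. A recalibrated version of the published fat-free-mass equation in athletes, against whichever DXA fat-free-mass definition is declared the reference. A proportional split leaves only about 23 of 33 athletes for this (33 × 0.7), so a single constant is realistic.

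Carry these fixed into the validation sample. For the fat equations, report bias and RMSE for published RFM, the updated versions and the new equation in the same people, on one scale (fat mass = percentage × body mass/100). Give a paired interval for the RMSE difference descriptively. State that any advantage of a new equation will be interpreted against the recalibrated existing equation as well as the published one. A formal superiority test should not be imposed: 39 people are too few to carry it.

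The cost is a few small regressions and some sentences of text, with no new participants or measurements. The downside is slightly more analysis, and the new equation's apparent advantage may shrink.

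### Selection of the new equation waits on an assumptions check that names an order-dependent Durbin–Watson test, with no row order defined, and two normality tests that unbiased prediction does not need

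*Protocol article*

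**What the plan says.** Section 2.1 fixes the design: "This will be a cross-sectional study based on the Strengthening the Reporting of Observational Studies in Epidemiology–Nutritional Epidemiology (STROBE–nut) guidelines". Section 2.7 states that "a total of 130 participants will be needed" and splits them 70/30 into development and validation samples.

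Section 2.8 then names these diagnostics for the new regression equations:

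- Multicollinearity: "Variance inflation factors will be used to detect multicollinearity among predictors in the multiple linear regression models".
- Independence of errors: "autocorrelation in the residuals will be assessed through the Durbin–Watson test".
- Normality: "normality of residual errors will be confirmed with the Omnibus k-squared and Jarque-Bera tests".

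After ranking the candidate models on AIC, BIC, Mallows' Cp and Hocking's Sp, the section makes selection conditional: "After compliance with all of the assumptions of the multiple regression analysis", "the model with the better performance that includes WG will be selected for further analysis". The normality tests stand in a parenthesis inside that sentence. Durbin–Watson stands in an earlier sentence. No significance level, row order or action on failure is given.

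**The concern.** The purpose is a prediction equation, to be judged on RMSE, agreement coefficients and Bland–Altman limits in a held-out sample. Two of the stated checks do not serve that purpose.

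Durbin–Watson is built from differences between adjacent residuals. It needs an order that means something, such as time or session. Without one, the same participants and the same fitted equation can give different values according to how the data file happens to be sorted.

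Normality of residuals matters for exact small-sample inference and for normal-theory limits. It is not needed for least-squares coefficients or predictions to be unbiased. A model can therefore predict best and still fail a normality test through mild skew.

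If the condition is applied literally, a better-predicting equation could be passed over for reasons unrelated to how well it predicts. The named tests also respond weakly to spread that grows with the fitted value, which is the feature that most affects a single SEE and a single pair of 95% limits.

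**Working it through.** The plan gives no figure to reproduce here.

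**Inputs from the protocol.** N = 130 and a 70/30 split (Section 2.7), so the development sample is 0.70 × 130 = 91 and the validation sample is 39. Models have at most three predictors (Section 2.8).

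**Assumed inputs.** Predictor distributions, a residual SD of about 3 units, the degree of skew, the pattern of variance and a 5% level for every test. None of these is in the protocol.

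**1. Order dependence of Durbin–Watson.** The statistic is DW = Σ(eᵢ − eᵢ₋₁)² / Σeᵢ². For independent residuals its mean is about 2 and its variance about 4/n. At n = 91 the SD is √(4/91) = 0.21, so the central 95% range is 2 ± 1.96 × 0.21 = 1.59 to 2.41. Shuffling one fixed set of 91 residuals 10,000 times gave 1.60 to 2.40 (central 95%), with extremes of 1.26 and 2.75. Sorting the same residuals by size gave 0.01. The same data can therefore pass or fail on row order alone.

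An order can be informative. With rows sorted by stratum and an omitted stratum effect of 1.5 or 3 units per step, the test rejected in 18% or 88% of runs, against 4–5% in random order.

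**2. A correct model under a 5% condition.** With normal, constant-variance errors the rejection rates were 4.4% (Durbin–Watson), 4.2% (Jarque–Bera) and 5.9% (Omnibus). The chance of failing at least one cannot exceed 4.4 + 4.2 + 5.9 = 14.5%. If every Jarque–Bera rejection is also an Omnibus rejection, and Durbin–Watson is independent of both, it is 1 − 0.956 × 0.941 = 10.0%. Direct simulations gave about 10%, 12% and 13%, in line with these values.

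**3. Mild skew.** The skewness part of Jarque–Bera is n × S²/6. With an assumed S = 0.6 this is 91 × 0.36/6 = 5.46. The 5% critical value on 2 degrees of freedom is −2 ln 0.05 = 5.99. Skew of that size therefore puts the test close to its threshold. Simulated failure of at least one test was 44%, 45% and 46%. A different set-up, taking the AIC-best waist-girth model, gave 31% (10% with normal errors). There the median RMSE loss from moving to another model was about 1.0 with skewed errors, and 0.16 against an RMSE of about 3.4 with normal errors.

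**4. What the named tests see if spread grows with the mean.** Residual SD is taken proportional to mean^g, and coverage is that of ±1.96 SEE.

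| g | Durbin–Watson | Normality tests | Breusch–Pagan | Coverage, low-fat third | Coverage, high-fat third |
|---|---|---|---|---|---|
| 0 | 4% | 4–6% | 4–5% | 94% | 94% |
| 0.5 | 4% | 7–8% | 18% | 97% | 91% |
| 1 | 4% | 18–19% | 60% | 99% | 88% |

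Other assumed settings gave 39–42% for the normality tests and 76–90% for Breusch–Pagan. The size depends on the scenario; the ordering does not.

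**The case against.** The case for leaving the text alone has real force.

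- **Durbin–Watson is not named in the condition.** It appears earlier, beside the variance inflation factors, as something to be assessed. It enters the selection step only through the general reference to all assumptions. This stands, so the text does not support reading the protocol as explicitly rejecting models on Durbin–Watson.
- **No discard rule is printed.** Compliance could be reached by transformation or re-specification. This also stands: the failure rates above apply only if the condition is run as 5% tests.
- **Durbin–Watson is not meaningless in every file.** Measurement spans two semesters, two sites and three strata, and an order by any of these could reveal grouping. This is correct. The defect is that no order is defined.
- **A reader might infer that the absence of a named constant-variance test is itself an error.** The documents do not support that. Constant variance falls under the same general reference to all assumptions, and a condensed article may leave the specific test to the full plan. The planned Bland–Altman diagrams would also show error growing with level.
- **A reader might also infer that unequal spread is the likely violation for fat mass in kilograms.** The model-building text gives no unit, and no figure in the protocol establishes unequal spread. It is plausible, no more.

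What survives is that Durbin–Watson without an order, and normality as a condition for selection, are stated choices rather than omissions.

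**Conclusion.** The point holds in limited form. Section 2.8 prescribes an order-dependent test for participants whose order it does not define, and makes selection follow an assumptions check that includes normality testing. The Durbin–Watson result is arbitrary as the text stands. If the condition is applied at 5%, a correct model fails at least one test in about 10–13% of samples, and in about 44–46% at an assumed skewness of 0.6 (31% in the alternative set-up). These rates rest on n = 91, three predictors, assumed distributions and an alpha that the protocol does not state.

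The consequence is minor to moderate. Least-squares coefficients stay unbiased under skewed or unequal-variance errors, and the chosen equation is still tested in the validation sample. The harm is the possible arbitrary exclusion of a better-predicting model and, if spread is unequal, one SEE and one pair of limits that suit neither end of the fat-mass range.

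**What to change.** In Section 2.8:

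1. Delete Durbin–Watson, or state the order in which it is computed (stratum, site or measurement session) and what it is meant to detect.
2. Report the Omnibus and Jarque–Bera results descriptively, and state that no ranked model is excluded on a diagnostic p-value.
3. Name a residual-versus-fitted plot, optionally with a Breusch–Pagan test, as the diagnostic that bears on the SEE and the 95% limits. If spread grows with the fitted value, report level-dependent limits.

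This takes a few sentences and a little extra analysis, with no new data. The drawback is a slightly more complex presentation of the limits if variance proves not to be constant.
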